### Sample size estimation

Approximately 44,000 residents of BC give birth each year [86]. We are seeking a sample of 1,000 participants for each of the two study time points. This will provide 80% power to detect AUC for ROC curves ≥ 0.56 as significantly different from 0.5, at a significance level = 0.05; 88% power to detect sensitivity ≥ 0.60 as > than 0.5; and > 99% power to detect specificity ≥ 0.60 as > 0.5. We will be able to estimate the prevalence of low prevalence conditions (e.g., 3%) with 1.5% margin of error and 95% confidence. Of note, we will have 80% power to detect AUC ≥ 0.65; 80% power to detect sensitivity ≥ 0.72; and 99% power to detect specificity ≥ 0.72. Allowing for an anticipated attrition of 15%, we are seeking to recruit 1,200 participants. To have 80% power to detect sensitivity ≥ 0.7; and 99% power to detect specificity ≥ 0.6 for the individual AD, we will need ≥ 30 participants per AD in this sample.

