### Objectives

The core objective of this research is to identify one or more accurate screening tools to detect perinatal AD. To this end, we will:Assess the accuracy of a range of screening tools for perinatal AD as a whole and individually. Specifically, we will report the full composite of screening tool metrics for each evaluated measure:i)at each assessment point (prenatal and postpartum);ii)for the core DSM-5 anxiety disorders alone, and including OCD and PTSD;iii)for each of the individual AD; andiv)across parity (parity = 0, parity ≥ 1) and major ethnic groups.Based on the above, we will report the most accurate screening tool for the AD as a group, and for each individual AD.

Secondary and exploratory study objectives:Document the prevalence of perinatal AD in pregnancy and the postpartum. As this study requires an unselected/representative sample of perinatal people from within a specified geographical region, it provides the opportunity for us to document prevalence.Explore relationships between participant demographic characteristics (e.g., age, relationship status, race/ethnicity, household income, income needs, education, employment status, geographical area of residence), identity (gender, sexual orientation), experiences with discrimination (e.g., race, social class, religion, weight/body size, chronic illness, history of substance use), and sleep with AD.Assess perinatal people’s experience with mental health assessment and treatment seeking and utilization. Among participants who reported symptoms meeting criteria for one or more AD, we will assess assessment and treatment seeking as well as any barriers experienced (e.g., cost, location, race or culture, time, etc.). Among those who received an assessment or treatment, we will ask about the nature, duration, and costs associated with any assessments or treatment received, as well as diagnoses obtained, and practitioner type.Assess the relationship between unpaid domestic labour (i.e., household chores and childcare responsibilities) and mental health and relationship satisfaction. Specifically, we will assess the overall burden (i.e., quantity), perceptions of fairness, and gender distribution of unpaid domestic labour with respect to mental health and relationship satisfaction prenatally and postpartum.

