#### Research objectives

AUC will be compared among all pairwise combinations of tools using DeLong’s method for paired ROC curves [123] and using a false-discovery-rate correction (FDR, with family-wise alpha = 0.05) for *p*-values [124] to account for multiple testing. Sensitivity and specificity will be compared across all tools using McNemar’s test for paired categorical data, with FDR correction for multiple testing [124].

We will report the full composite of the screening tool metrics (i.e., AUC, *J* index, PPV, NPV, LR + , and LR-) for each of the measures assessed. Screening metrics will be reported for the core AD with and without PTSD and OCD, as well as separately for major ethnic and parity groups (i.e., parity = 0, and parity ≥ 1). We will recommend screening tools based on their accuracy (i.e., scores on the above metrics) and implementation feasibility (i.e., length, administration time, scoring time and complexity, and cost, if any). To ensure the screening tools are not missing any individual AD by analyzing them together, we will also estimate sensitivity and specificity for each AD by comparing those who report symptoms meeting criteria for one specific AD with those whose symptoms fail to meet criteria for any AD.

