The study includes a number of additional methodological strengths. Specifically, the study is powered to ensure we can assess the accuracy of included screening tools both for the AD as a whole, but also for each individual AD. Our approach to recruitment is designed to result in data for 1,000 pregnant and 1,000 postpartum people. We are over-sampling, where needed, perinatal people with specific AD so that we are able to report on screening accuracy for each of the individual AD.

Beyond the core goal of this research (i.e., to assess the accuracy of various self-report measures when used as screening tools for perinatal AD), we have the opportunity to explore a number of additional research questions. For example, because this research is based on DSM-5 anxiety and related disorders, we are also able to explore screening for separation anxiety disorder. To our knowledge, no findings related to screening for adult separation anxiety among perinatal people have been published. In addition to providing information about screening accuracy for adult separation anxiety disorder, we will also be able to provide the first estimate of the prevalence and incidence of this condition among perinatal people. Further, we will document the point prevalence and postpartum incidence of perinatal AD in pregnancy and the postpartum. To our knowledge, perinatal AD prevalence, based on DSM-5 criteria has yet to be reported. Further, we will be able to assess the extent to which participants who report symptoms meeting criteria for one or more AD go on to receive an assessment and treatment for these conditions. We will also assess various predictors (e.g., demographic, reproductive, identity, experience of discrimination) of perinatal AD symptoms and diagnosis, as well as assessment and treatment access and utilization. Finally, we will assess the relationship between the burden and gender distribution of unpaid domestic labour (i.e., household chores and childcare responsibilities) and mental health.

Findings from this research will provide rich data to answer not only our core research questions but additional, important questions pertaining to perinatal AD.

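### The stated power is for a single tool tested against 0.5, a test the analysis plan does not contain; it does not describe power to separate tools, and about 30 cases cannot support naming one most accurate tool per disorder

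*Protocol article*

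**What the plan says.** - Protocol article, Sample size estimation, on the target of 1,000 people at each time point: "This will provide 80% power to detect AUC for ROC curves ≥ 0.56 as significantly different from 0.5, at a significance level = 0.05". Against the same value of 0.5, a sensitivity of 0.60 is credited with 88% power and a specificity of 0.60 with more than 99%. A later sentence gives 80% power for AUC of at least 0.65 and for sensitivity of at least 0.72, without a comparator or a number of cases. The last sentence gives 80% power for sensitivity of at least 0.7 with at least 30 participants per disorder.
- Data analysis plan, Research objectives, on AUC, with FDR correction: "AUC will be compared among all pairwise combinations of tools using DeLong’s method for paired ROC curves". The same section treats the other two accuracy measures in a similar way: "Sensitivity and specificity will be compared across all tools using McNemar’s test for paired categorical data, with FDR correction for multiple testing". The recommendation rests on the metric scores plus feasibility.
- Objectives: "we will report the most accurate screening tool for the AD as a group, and for each individual AD".
- Introduction: the minimum standard for a tool worth implementing includes AUC of at least 0.8 and Youden's J of at least 0.5.
- Discussion, in a sentence that goes on to name the disorders taken one by one: "the study is powered to ensure we can assess the accuracy of included screening tools both for the AD as a whole, but also for".

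**The concern.** The sample size section and the analysis plan answer different questions. The first asks whether a single tool does better than 0.5. The second compares tools with each other, on the same people, with a multiplicity correction. No stated power figure contains a difference between tools, a between-tool correlation or a correction.

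Beating 0.5 also says little about the decision. Tools entered on evidence of accuracy already had to show AUC of at least 0.70 or 0.75 (the section on anxiety disorder screening measures gives both) and J of at least 0.40, and the standard for use is higher still.

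What is at stake is how the results are read. If 80–88% is taken as power to tell tools apart, a non-significant pairwise result could be misread as equivalence. A single named tool per disorder could then rest largely on chance ranking.

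**Working it through.** **Inputs.** N = 1,000 per time point and at least 30 cases per disorder (Sample size estimation). AD prevalence about one in five (Introduction), giving 200 cases and 800 non-cases; the sample size section does not state its prevalence, so this is an assumption. Table 1 lists nine screening measures, hence 9 × 8 / 2 = 36 pairs. Between-tool correlation r is not given and is varied from 0.3 to 0.7.

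**1. Reproducing the plan's figures against 0.5.**

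Proportion: power = Φ{[(p − 0.5) − z·√(0.25/n)] / √(p(1 − p)/n)}.
- Sensitivity 0.60, n = 200: 88.6% one-sided, 81.2% two-sided. Stated 88%.
- Specificity 0.60, n = 800: above 99.9%. Stated above 99%.
- Sensitivity 0.72, n = 30: 80.3% one-sided, 69.2% two-sided. Stated 80%.
- Sensitivity 0.70, n = 30: 72.4% one-sided (exact binomial 73.0%), 60.0% two-sided (exact 58.9%). Stated 80%. **This one does not reproduce.**

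AUC: null SE = √[(n1 + n0 + 1)/(12·n1·n0)].
- 200/800: SE = √[1001/(12 × 200 × 800)] = 0.0228. The AUC detectable with 80% power is 0.5 + (1.96 + 0.84) × 0.0228 = 0.564 two-sided, or 0.557 one-sided. Both round to the stated 0.56.
- 30/970: SE = 0.0535, so 0.5 + 2.80 × 0.0535 = 0.650 two-sided, as stated.

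Apart from the 0.70 figure, the set is consistent with one-sample tests against 0.5. The 0.60 and 0.72 sensitivity figures fit only as one-sided tests, whereas AUC 0.65 fits as two-sided.

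**2. The planned kind of test, AD as a whole.** Hanley–McNeil SEs with 200/800: 0.0197 at AUC 0.80 and 0.0177 at 0.85. SE of the difference = √(s1² + s2² − 2·r·s1·s2); power = Φ(0.05/SE − z). FDR lies between alpha 0.05 and its strictest step, 0.05/36 = 0.0014.

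| r | SE of difference | Power at 0.05 | Power at 0.05/36 |
|---|---|---|---|
| 0.3 | 0.0222 | 61% | 17% |
| 0.5 | 0.0188 | 76% | 30% |
| 0.7 | 0.0146 | 93% | 59% |

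The smallest gap above AUC 0.80 detectable with 80% power is 0.053 (r = 0.5) or 0.042 (r = 0.7) at 0.05, and 0.075 or 0.059 at 0.05/36.

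**3. The same gap with 30 cases.** SEs are 0.049 and 0.044, almost identical with 800 or 970 non-cases. Power is 15%, 19% and 28% at 0.05 for r = 0.3, 0.5 and 0.7, and 1%, 2% and 3% at 0.05/36.

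**4. Precision.** 95% half-width for AUC 0.80: 1.96 × 0.0197 = 0.04 with 200 cases and 1.96 × 0.049 = 0.10 with 30. For sensitivity near 0.70 to 0.75: about 0.06 and 0.16.

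**5. Against the adequacy bar.** Take as one illustration a lower 95% limit above 0.80 when the true AUC is 0.85. With 200 cases: Φ(0.05/0.0177 − 1.96) = 81%. With 30: Φ(0.05/0.0444 − 1.96) = 20%.

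**The case against.** The best defence is that the pairwise tests do not decide anything alone. Research objectives bases the recommendation on metric scores and feasibility, and the core objective is to find one or more accurate tools. That stands. A reader might infer that the tests pick the winner, but the document does not say so; they support a ranking.

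A reader might also infer that paired, corrected tests must have less power than stated, or that 1,000 is too few. Neither follows. Paired power depends on a correlation the document does not give; overlapping content (the K6 is part of the K10) would favour a high one. The 0.05/36 column is a floor, since FDR is usually less strict. For a wider gap, AUC 0.78 versus 0.86, power is about 85% at r = 0.5 even at that floor.

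The Discussion claims power to assess accuracy, not to rank tools, and the headline figures print their comparator. For single disorders the data analysis plan speaks of estimating sensitivity and specificity and does not explicitly extend the pairwise tests to them. Thirty is a minimum, and over-sampling is mentioned. All fair. But Objectives still promises one most accurate tool for each disorder, and estimates with a half-width of 0.10 cannot order tools of similar accuracy, whether or not a test is run.

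Finally, an article may leave detectable differences to a fuller document. Here, though, it does print a justification, and that justification does not match the analysis it prints.

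**Conclusion.** The point holds as a mismatch. The power figures describe one tool against 0.5, stated for the first set and implied for the later ones, while the planned tests compare tools and the adequacy standard is far above 0.5. The 80–88% therefore says nothing about separating tools or showing that one is adequate.

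For AD as a whole, N = 1,000 is not shown to be insufficient: power for AUC 0.80 versus 0.85 may fall above or below 80%, depending on the correlation and the FDR step reached. For a single disorder with about 30 cases, power for that gap is 28% at most over the range examined, so a single most accurate tool per disorder is not supported. Separately, the 80% for sensitivity 0.7 with 30 cases is too high by 7 to 8 points one-sided and about 20 points two-sided.

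The paired results rest on an assumed prevalence of 20%, r of 0.3–0.7, an illustrative AUC gap of 0.05 and Hanley–McNeil variances.

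**What to change.** Keep N, the data and the tests.

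- **Sample size estimation:** say that the figures are single-tool power against 0.5 and state their sidedness. Correct the figure for sensitivity 0.7 with 30 cases. Add the smallest paired differences in AUC and sensitivity detectable with FDR correction over a stated correlation range. Add the expected 95% half-widths: AUC about 0.04 with 200 cases and 0.10 with 30; sensitivity about 0.06 and 0.16.
- **Discussion:** limit the per-disorder claim of being powered to estimation with that precision.
- **Objectives and Research objectives:** for individual disorders, report paired differences from the top-ranked tool with 95% confidence intervals. Name the set of tools not distinguishable from it, in place of one most accurate tool.

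The cost is rewording and a short calculation, with no extra participants. The price is that the stated power looks less favourable and the per-disorder conclusions become more cautious.

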### Ethics

#### Ethics approvals

Approval for this study has been granted by the University of British Columbia’s Behavioural Research Ethics Board (#H20-01277).

#### Ethical and safety considerations

At the start and end of each questionnaire, all participants are provided with a list of pregnancy and postpartum-related resources in their community. During study interviews, any participant who reports clinically significant symptoms, or symptoms meeting diagnostic criteria for one or more AD, are provided a list of treatment services in their community, as well as individualized referral suggestions from the study interviewer.

If it is determined that a participant is suffering from suicidal ideation, additional steps are taken to ensure participant safety. If a participant endorses suicidal ideation during the completion of the online questionnaire (i.e., answers ‘Yes, quite often,’ or ‘Sometimes,’ to: “The thought of harming myself has occurred to me.”) on the measure administered to assess depressed mood (i.e., the Edinburgh Perinatal Depression Scale) [43], an additional risk assessment questionnaire then probes for suicidal behaviour. If a participant is deemed to have elevated risk for suicidal behaviour, the study team is alerted, and the participant is contacted via phone by a trained team member within 24 hours. If no contact is made, a follow up email is sent to maximize earliest participant contact. If suicidal ideation is identified during a study interview, the interviewer takes the necessary steps to ensure the participant’s safety. Management of suicidal ideation is based on the study safety and emergency mental health protocol.

In the event of a perinatal loss, participants are contacted by a member of the study team to express support, and perinatal loss specific resources are provided if desired with the option for additional support or resources at a later time, if needed. Only data provided prior to a perinatal loss will be retained in the data set (e.g., in the event that a loss occurs following the completion of the prenatal questionnaires and interview, data will be retained).

### Data collection and storage

Study questionnaires are completed online via REDCap [87, 88], and study interviews are administered by telephone or Zoom video conferencing [89].

#### Consent

Consent for this project is provided electronically at the time of enrollment. Interested individuals are able to access the study intake form from advertisements and are able to follow links to the consent form and eligibility questionnaire. Upon providing consent, participants are then able to download and save a PDF copy of the consent form for their personal records. By consenting to participate, participants are also consenting to complete the study interviews. Participants are informed of limits to confidentiality (i.e., urgent risk of harm to oneself, or harm coming to a child) in the consent form and at the beginning of each interview.

Consent for recording the interviews (for the purpose of assessing inter-rater reliability) is requested verbally at the beginning of each interview.

#### Participant communication

Personal, identifying information (e.g., name, first three digits of postal code, telephone) is acquired via the study intake form and stored in REDCap. For the duration of participation in the study, first name and email address of the participants remained connected in REDCap along with a unique ID code in order to send participants questionnaire links, reminders, and other communication throughout participation in the study.

#### Protection of participant information

Once data collection is complete, all data will be downloaded and stored on a secure, password-protected University of Victoria computer server, and subsequently deleted from the REDCap server. At that time, all identifying participant information will be removed from the study data files, and data will be identified only by a unique ID code only. Participant contact information, along with ID codes, will be stored on a separate, password protected file to retain participant information for future contact and potential follow up surveys.

### Procedures

Following study enrollment, participants are administered questionnaires and an interview at two time points: once prenatally and once postpartum. Each assessment consists of online questionnaires and a semi-structured diagnostic interview. Participants are emailed a link to the questionnaires which they complete online. Prenatal questionnaires are completed between 16- and 32-weeks’ gestation. Postpartum questionnaires are completed between 6 and 16 weeks postpartum. All interviews are conducted over the phone or by video conference, 2–6 weeks after the completion of the questionnaires. See Fig. 1 for diagram of participant flow through the study.

**Fig. 1 Fig1:**
[figure not shown]
Participant flow

### Assessment tools

See Table 1 for a summary of study measures.

**Table 1 Tab1:** Summary of study measures

Domain	Measure	Method	Location
*Intake*			
Consent			Online
*Prenatal Questionnaire (16–32 weeks’ gestation)*			
Characteristics	Demographic and reproductive history information	Self-report	Online
AD Screening Measures	Perinatal Anxiety Screening Scale (PASS) State-Trait Anxiety Inventory (STAI-Y2) Edinburgh Postnatal Depression Scale (EPDS) Kessler Psychological Distress Scale (K6/K10) Matthey Generic Mood Questionnaire (MGMQ) Antenatal Risk Questionnaire (ANRQ-2A) Generalized Anxiety Disorder (GAD-7) Anxiety Disorders 22 (AD-22) Perinatal Anxiety Screening Questionnaire (PASQ)	Self-report	Online
Other functioning	Insomnia Severity Index (ISI) Covid-19 experience Family Work Quality Questionnaire (FWQQ)	Self-report	Online
*Prenatal Interview (2-4 weeks after prenatal questionnaire completion)*			
Diagnosis and onset (ADs, OCD, PTSD)	Diagnostic Assessment Research Tool (DART for DSM-5-TR)	Diagnostic Interview	Zoom or phone
*Pregnancy Check-In*			
Characteristics	Pregnancy status and birth date	Self-report	Online
*Postpartum Questionnaire (6–16 weeks postpartum)*			
Characteristics	Birthing information	Self-report	Online
AD Screening Measures	Perinatal Anxiety Screening Scale (PASS) State-Trait Anxiety Inventory (STAI-Y2) Edinburgh Postnatal Depression Scale (EPDS) Kessler Psychological Distress Scale (K6/K10) Matthey Generic Mood Questionnaire (MGMQ) Antenatal Risk Questionnaire (ANRQ-2A) Generalized Anxiety Disorder (GAD-7) Anxiety Disorders 22 (AD-22) Perinatal Anxiety Screening Questionnaire (PASQ)	Self-report	Online
Other functioning	Insomnia Severity Index (ISI) Covid-19 experience Family Work Quality Questionnaire (FWQQ) Mental health support seeking	Self-report	Online
*Postpartum* *Interview* *(2-4 weeks after prenatal questionnaire completion*)			
Diagnosis and onset (ADs, OCD, PTSD)	Diagnostic Assessment Research Tool (DART for DSM-5-TR)	Diagnostic Interview	Zoom or phone

#### Diagnostic interviews

##### **Diagnostic Assessment Research Tool (DART)** [90]

The DART is a psychometrically sound, semi-structured diagnostic interview designed to assess of a wide range of mental health conditions within the Diagnostic and Statistical Manual of Mental Disorders – 5th edition – Text Revision (DSM-5-TR) mental health conditions, including all the anxiety and anxiety-related disorders [90]. The DART includes mandatory, criterion-based questions and optional questions that may be necessary for clarification in order to make a diagnosis. Psychometric testing of the DART demonstrates excellent construct validity and good convergent and discriminant validity, and high interrater reliability [91]. The DART is used in this study to assess: (a) all DSM-5-TR anxiety disorders, (b) OCD, (c) PTSD, as well as (d) disorder age of onset and relation to reproduction. To assess perinatal AD specifically, the DART interview has been tailored to include perinatal specific examples (e.g., fear of childbirth, perinatal-related obsessions, birth trauma).

##### Interview training

Our team has extensive experience training students to administer diagnostic interviews to perinatal research participants. All study interviewers are trained to a strict criterion. Specifically, they are required to match the supervising interviewer: (a) on the primary diagnosis, and (b) to within ± 0.5 severity point, on two successive interviews to be permitted to interview independently. Study interviewers are also trained in special considerations in the assessment of perinatal AD, and the assessment of perinatal specific symptoms of the AD (e.g., worries about the baby, fear of childbirth). Study interviewers are closely supervised throughout the study.

